### Brief cognitive analytic therapy

Brief CAT will be delivered across eight 50–60 min sessions, typically on a weekly basis, following an established 8-session protocol [15, 47] that has been written to reflect the standard tri-phasic reformulation, recognition, and revision CAT approach. The therapy will focus on self-harm but will also seek to identify and work with the underlying processes that contribute to self-harm, including relational roles and patterns. Sessions 1–2 focus on *reformulation*, where a shared understanding of a young person’s difficulties is developed. Session 3 is where the narrative reformulation is delivered (i.e. start of the recognition phase). Sessions 4–5 further focus on *recognition*, where a young person is supported to better notice unhelpful patterns and roles in their day-to-day life. Sessions 6–8 then focus on revision, where ‘exits’ from unhelpful patterns and roles are identified and practised. Throughout CAT, there is a focus on the therapeutic relationship, including the potential enactment of patterns here that could occur elsewhere in a young persons’ life. A follow-up session is arranged approximately 4 weeks following the final session to help consolidate therapy gains and problem solve remaining issues.

Sessions will take place either in person or online via video call. Therapy will be delivered by a qualified psychological therapist (e.g. clinical psychologist, counselling psychologist) at band 7 or 8 who has completed CAT practitioner training. Supervision will be provided at least fortnightly by a CAT accredited supervisor and CAT psychotherapist. Fidelity will be assessed by rating a random 10% subset of sessions using the Competency of Cognitive Analytic Therapy measure (CCAT; [48]) by an independent expert. The CCAT is widely used for determining the competency of CAT. An adherence checklist will also be kept by therapists and reviewed in supervision. Supervision will also involve listening to recordings of sessions to ensure adherence and competency.

Participants will be asked to complete sessional tracking forms at each session that focus on the recognition and revision of idiographic target problems (TPs) and target problem procedures (TPPs). These tracking forms are used as part of the therapy to guide and focus the work taking place. These forms will be collated and analysed to investigate idiographic change amongst participants receiving brief CAT. Participants in the brief CAT arm will be asked to complete the session rating scale [49], a measure of perceived working alliance, at the end of therapy.

### Treatment as usual

TAU will follow standard care provided by CAMHS. There is often no standard pathway for young people who self-harm. Instead, the level and nature of input varies depending on factors such as risk and perceived need. TAU might commonly include:Assessment and formulation with a clinicianRisk assessment and management with a case manager or partnership workerOne-to-one work on emotion regulation (this may be using a non-standardised model)Group emotion regulation skills sessionsStructured psychological therapies (e.g. CBT, DBT) as recommended by NICEFamily therapy/systemic family practice

A patient would rarely get offered all of these, and higher-intensity interventions such as CBT, DBT, or family therapy are less likely to be offered. Within the trial, participants in both groups will be able to continue to access medication, support groups (that do not adopt a structured psychological model), and safety planning (including meetings with a case manager or partnership worker), and psychiatric support as routinely provided by services. For participants allocated to the brief CAT arm of the trial, it would be clinically contraindicated to offer another high-intensity, 1-to-1, talking therapy that occurs at the same time as the brief CAT sessions, however. Access to health and social care services and interventions will be carefully monitored as part of the trial. We will record what TAU typically involves, using the bespoke service use measure described above, which will inform the development of a health economic workstream for the definite trial. We will not be offering any additional care following each participant’s involvement in the trial.

### Data collection

Assessment sessions will take place with a researcher either in person or online via video call or telephone. In person sessions might take place in a participant’s home, school, CAMHS offices, university, or other NHS building. Allowing flexibility in the modality of assessments may aid engagement and retention. Researchers will administer questionnaires and interviews and support the young person to answer questions as needed. Data will be collected via a case report form (CRF). A copy of the CRF, excluding copyrighted material, is available on request. Researchers will receive training in delivering assessments and regular, at least fortnightly, supervision.

Participants and services will also receive a newsletter that will update them on news about the trial and thank them for their involvement. This may aid engagement and retention, especially amongst those in the TAU arm, but helping them to feel a part of the trial between contacts. Participants will be free to withdraw from the trial at any time. If they are in the brief CAT arm, they may choose to end therapy early but continue with the research components of the trial. Where participants choose to leave therapy or the trial early, they will be asked for their reasons for leaving, to aid us in identifying possible barriers to engagement.

### Qualitative process evaluation

The qualitative process evaluation will enable an in-depth investigation of trial acceptability and the identification of potential therapy mechanisms of action. Qualitative interviews with stakeholders including clinicians and parents are also planned as part of a linked, parallel study. Participants from both arms of the trial will be invited to take part in qualitative interviews (*n* = 15 from brief CAT arm; *n* = 5 from TAU arm). A larger subsample from the brief CAT arm will be sought to allow more exploration of perceived therapy impact and mechanisms or action. Sample size targets have been guided by the principles of information power [50]. Given the relatively narrow focus of the study, the specific population of interest, and the expectation of in-depth data based on similar studies [51, 52], a sample of 20, which is common for process evaluations of this nature, has been chosen [19, 53].

Participants will be sampled from the main trial with their consent. Maximum variation sampling will be used to create a diverse sample with regard to trial retention (i.e. whether people withdraw early or not), gender, age, neurodiversity, and ethnicity. This will be achieved by inviting participants sequentially to be interviewed and monitoring the characteristics of this subsample as it develops, so that the choice of the next person to be invited can be informed by these characteristics. A semi-structured schedule will guide interviews. The interview schedule will be developed with people with lived experience involved and guided by the theoretical framework for acceptability of healthcare interventions [54]. The interview schedule will be piloted. Interviews will be audio recorded on an encrypted device to aid transcription. Interviews are expected to last up to 60 min and could take place in person or remotely via video call.

The researcher undertaking qualitative interviews will have experience of qualitative research and will have received training in qualitative methods. They will not have any past relationship with participants. The lead qualitative researcher will have a PhD in psychology or a related discipline. The Consolidated criteria for reporting qualitative research (COREQ; [55]) will be used when reporting qualitative results.

### Patient and public involvement

The trial has been designed with the involvement of young people with lived experience of self-harm, and those with lived experience will continue to be involved in the running of the trial. The trial team includes a co-investigator with lived experience of self-harm and a research assistant with lived experience. These individuals will contribute to management meetings and ensure the perspective of those directly affected by self-harm is taken into account. A PPI advisory group consisting of young people with lived experience of self-harm will also meet four times a year, providing guidance and informing decision-making during the trial.

### Safety monitoring and reporting

AEs and serious adverse events (SAE) will be monitored and recorded throughout the trial. SAEs will include events that result in death, are life-threatening, or result in hospitalisation. This will therefore include some but not all instances of self-harm. AEs related to self-harm behaviour and ideation, interpersonal conflict, and deterioration in mental health are expected. The research team will review all SAEs to determine the probability that the event is causally linked to study procedures or interventions based on available data (e.g. timing of event and participant report on antecedents). The TSC will have access to SAE reports and will provide independent monitoring of SAEs throughout the trial. The TSC will also monitor the overall number of AEs and SAEs occurring during the course of the trial. An imbalance in AEs and SAEs between trial arms is expected due to factors such as random variation and the increased participant contact for those in the brief CAT arm (i.e. AEs may be more readily identified due to the regular appointments). Any substantial imbalance will require a review.

Therapy may be discontinued in cases where this is required to maintain the safety of participants or others. Where SAEs are attributed to the trial procedures, this may be grounds to discontinue therapy or withdraw a participant from the trial altogether. A participant may be withdrawn if the research team are notified of a significant potential threat to the safety of a member of the research team or if a participant displays aggressive or abusive behaviour towards a member of the team. These decisions would be made in consultation with the participant’s clinical team, and the TSC, and would occur on a case-by-case basis. Where SAEs are attributed to the trial procedures, it may also be necessary to pause or stop the trial altogether, and such decisions will be made with the TSCs and the funder’s guidance.

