#### Self-harm behaviour and urges

The SITBI short form [28] is a structured interview measure that will be used to assess suicide attempts and non-suicidal self-injury (NSSI). Sections of the measure will be adapted in line with the revised version of the SITBI [35] to improve the clarity of questions. Specifically, the opening question about NSSI will use the wording from the revised SITBI that provides additional detail on what might be considered as NSSI and some examples of behaviours that would not count as NSSI including indirect forms of harm (e.g. starving oneself). The ABUSI [34], a 5-item questionnaire, will be used to assess urges to self-harm over the past week. Scores range from 0 to 30 with higher scores indicating more severe urges. The validity and reliability of both measures have been demonstrated with young people [28, 34].

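### Causality review and the pause/stop ground are stated for SAEs only, so a suicide attempt without threat to life or admission has no stated event-level attribution

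*Protocol article*

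**What the plan says.** All provisions below are in the protocol article; unless another section is named, they are in Safety monitoring and reporting.

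- Seriousness: "SAEs will include events that result in death, are life-threatening, or result in hospitalisation". The article draws the consequence itself: "This will therefore include some but not all instances of self-harm".
- Expectedness: "AEs related to self-harm behaviour and ideation, interpersonal conflict, and deterioration in mental health are expected".
- Causality: "The research team will review all SAEs to determine the probability that the event is causally linked to study procedures or interventions". No such step is described for non-serious AEs.
- Trial-level consequence: "Where SAEs are attributed to the trial procedures, it may also be necessary to pause or stop the trial altogether". A parallel sentence uses the same trigger for discontinuing therapy or withdrawing a participant.
- Aggregate monitoring: "The TSC will also monitor the overall number of AEs and SAEs occurring during the course of the trial", and, on differences between arms, "Any substantial imbalance will require a review".
- Participant report: the AEP questionnaire, once, at 20 weeks.
- Oversight (Trial management): a TSC subgroup acts as the DMEC and monitors AEs, and the TSC receives updates at least quarterly.
- Measurement (Self-harm behaviour and urges): the SITBI is a "structured interview measure that will be used to assess suicide attempts and non-suicidal self-injury (NSSI"). Table 2 schedules it at baseline, 8, 16 and 20 weeks, in both arms.

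**The concern.** Under the stated rules, whether an individual suicide attempt is examined for a link to the trial depends on threat to life or on admission. Admission partly reflects local practice and circumstances, not only the nature of the act. In adolescents enrolled because they self-harm, a suicide attempt is the event for which one would most want a documented judgement on whether therapy or assessment contributed.

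At stake is how the safety result can be read. A final report of no related SAEs would be taken as reassurance when a definitive trial is planned, yet it would say nothing about attempts below the seriousness threshold, because relatedness need not have been asked for them.

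**Working it through.** The article gives no safety rate, count or threshold, so there is no figure to reproduce. The check sets the provisions side by side.

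**1. Two attempts traced through the stated rules.** Assume the same act in both cases, not life-threatening, and that attendance without admission does not count as hospitalisation.

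| Step | Attempt followed by admission | Attempt treated and sent home |
|---|---|---|
| Meets a listed seriousness criterion | Yes (hospitalisation) | No |
| Class on the listed criteria | SAE | AE, of a kind declared expected |
| Event-level causality review stated | Yes | No |
| Individual report available to the TSC | Yes (SAE report) | Not stated; included in the overall number |
| Can meet the stated attribution-based pause/stop ground | Yes, if attributed | No |

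The two columns differ only in admission.

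**2. What else reaches the second attempt.**

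- *TSC monitoring of AE numbers.* This is a total. Entry requires at least two lifetime episodes of self-harm, one within the past year (Trial setting and participants), so a few attempts would be pooled with many other expected self-harm AEs.
- *Imbalance review.* It covers AEs as well as SAEs. The size that triggers it is not defined and its consequence is not stated. The article also says in advance that some imbalance is expected, from chance and from more frequent contact in the brief CAT arm. With 30 per arm, a comparison of totals does not answer whether a given attempt was linked to therapy.
- *AEP.* It asks about adverse experiences of taking part, but once, at 20 weeks, and no route from it into causality review is described. It also depends on follow-up. Table 1 rates retention at 16 weeks as green from 75%, so up to 60 × (1 − 0.75) = 15 participants could miss that assessment with retention still green. No criterion is set for 20 weeks.
- *Discontinuing therapy on safety grounds.* This does not need an SAE. It concerns one participant and produces no attribution judgement.

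Each route exists. None asks, for the individual attempt, whether it was related.

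**3. Is the information available?** Largely. The SITBI covers suicide attempts at each follow-up assessment in both arms. The article states no link from a SITBI report to the causality review.

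**4. Wording of the triggers.** Causality is judged against two things, study procedures and interventions. Both consequence sentences (discontinuing or withdrawing; pausing or stopping) name trial procedures alone. Read literally, an SAE attributed to the therapy itself meets neither.

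**5. Size.** The number of attempts expected, and the share below the threshold, are not in the article. The gap can be located but not quantified.

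**The case against.** The strongest reply has four parts.

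*Non-serious events are not ignored.* AEs are recorded throughout, a TSC subgroup monitors them, a substantial imbalance must be reviewed, therapy can be stopped for safety without an SAE, and the AEP gives participants a voice. A reader might infer that sub-threshold events can never be attributed to the trial or lead to a pause. The article does not say so: the pause sentence states what may follow attributed SAEs and does not bar the TSC from advising a pause on other grounds. This part of the reply stands, but these routes are aggregate, late or undefined and do not replace review of the event.

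*The list may not be closed.* The article says what SAEs will include, not that nothing else counts, and it condenses a fuller protocol (version II, 19/8/2025) that is not shown. That fits a qualified conclusion. It is also why a complaint that lasting injury or disability is missing from the list would not be secure, and why it cannot be said that SITBI-reported attempts are kept out of AE recording. Even so, the article states the criteria, the scope of the review and the trigger, and accepts that some self-harm falls outside; the gap follows from those statements together.

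*Attempts would not be hidden.* Descriptive statistics are planned by group for all potential outcome measures, which include the SITBI, and safety is not among the progression criteria in Table 1. Both are true. A count by arm is still not a relatedness judgement.

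*In this population single events are hard to attribute, so comparing arms is defensible.* This has force against requiring a relatedness judgement for every AE, which is not pressed here. It has less force for suicide attempts, a narrow class for which the causality procedure already exists.

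**Conclusion.** The point holds in a limited form. On the criteria the article lists, a suicide attempt that is neither life-threatening nor followed by admission has no stated event-level attribution and cannot meet the stated attribution-based ground for pausing or stopping. A report of no related SAEs could therefore coexist with related suicide attempts.

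It rests on two assumptions: that the three listed criteria are the ones applied, and that attendance without admission is not hospitalisation. The unseen full protocol may close the gap.

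A reader might go further and infer that most therapy-related self-harm escapes review. The article supports only that some does, and gives no proportion.

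The mismatch between the causality sentence and the two trigger sentences is a separate, smaller inconsistency. It is visible in the text and needs no assumption. The change is worth making because it bears on how the harm results can be read and costs little.

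**What to change.** In Safety monitoring and reporting:

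1. State that every suicide attempt, however it comes to light (SITBI at any follow-up in either arm, therapist, clinical team), goes through the same causality review as an SAE and is reported to the TSC subgroup, whether or not the participant was admitted.
2. Report these attempts by arm with the relatedness judgement. Because the article expects AEs to be noticed more readily in the brief CAT arm, also give the source of each report, so that attempts found by the SITBI, which has the same schedule in both arms, can be compared separately.
3. Reconcile the sentence on what causality is judged against with the two sentences on discontinuing or withdrawing and on pausing or stopping. Which scope applies is for the trial team and the TSC to decide; the three sentences should agree.
4. If the full protocol already covers any of this, a sentence in the article saying so is enough.

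The cost is protocol and form wording, some extra review work for the research team and the TSC subgroup, and a higher count of reviewed events, which the report should explain. Sample size and assessment schedule are unchanged.

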## Method

### Design, randomisation, and blinding

A single-blind feasibility RCT design will be undertaken whereby participants are randomly allocated on a 1:1 basis to either brief CAT plus TAU or TAU alone. Assessments will take place at baseline, 8-, 16-, and 20 weeks post-randomisation. Randomisation will take place after the baseline assessment and be conducted independently using SealedEnvelope.com, using a randomised block design (block sizes of 4 and 6 generated at random) that is stratified by site (NHS trust). Allocation concealment will be ensured by independent randomisation, with researchers involved in enrolling participants and assessment not having access to randomisation sequence. Members of the research team not blind to allocation will inform participants of their allocation. A flow chart of trial procedures is available in Fig. 1.

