### Sample size

We will aim to recruit *N* = 60 participants (30 per trial arm). This number will enable key outcomes of interest, linked to our progression criteria, such as retention rates, and key parameters to inform a power calculation for a larger trial, such as the standard deviation of clinical outcome measures, to be estimated with adequate precision and minimal bias [56, 57]. For example, Teare and colleagues [56] recommend a sample of 60 or more based on simulation results for estimating event rates. Note that we are interested in event rates across both arms for our progression criteria (i.e. we are not evaluating progression criteria separately for each arm).

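### The between-arm AE imbalance that goes to review is not tied to events captured alike in both arms, so extra detection in the CAT arm cannot readily be told from a true excess

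*Protocol article*

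**What the plan says.** Under Safety monitoring and reporting, the protocol article states that "AEs and serious adverse events (SAE) will be monitored and recorded throughout the trial". It lists the kinds of AE it anticipates: self-harm behaviour and thoughts, conflict with others, and worsening mental health. It defines SAEs by death, threat to life or hospital admission. The trial steering committee (TSC) follows the total counts of AEs and SAEs and has access to the SAE reports.

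The section then says that a difference between arms is to be expected. One reason is chance. Another is the greater contact in the CAT arm, where "AEs may be more readily identified due to the regular appointments". The next sentence is the between-arm signal: "Any substantial imbalance will require a review".

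The contact schedule is set out elsewhere. For both arms, under Design, randomisation, and blinding: "Assessments will take place at baseline, 8-, 16-, and 20 weeks post-randomisation". For the CAT arm only, under Brief cognitive analytic therapy: "Brief CAT will be delivered across eight 50–60 min sessions, typically on a weekly basis", and "A follow-up session is arranged approximately 4 weeks following the final session".

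**The concern.** The plan names a detection difference between the arms and then uses the count affected by it as its between-arm safety signal. It does not say that events found only at therapy sessions are identified as such, or that any comparison is made on sources common to both arms.

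This works in two directions. Extra detection in CAT can produce an apparent excess when none exists. A real excess in CAT would come with a benign explanation already written into the protocol, and the article describes no between-arm count against which to test that explanation. The anticipated non-serious events are of a kind that often comes to light only when someone asks. The participants are 13 to 17 years old, and a TSC subgroup takes the place of a separate data monitoring committee (Trial management), so the counts it sees should be interpretable. A definitive trial is also likely to inherit the AE procedures tested here.

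**Working it through.** **Is there a figure to reproduce?** No. The article gives no AE rate, no detection rate and no threshold for a substantial imbalance. The check is therefore a count of contacts followed by an illustration on stated assumptions.

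**Step 1: scheduled trial contacts after randomisation (from the article).**
- Both arms: assessments at 8, 16 and 20 weeks = 3.
- CAT only: 8 sessions + 1 follow-up session = 9.
- Totals: TAU 3; CAT 3 + 9 = 12.

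With weekly sessions the follow-up falls at about 8 + 4 = 12 weeks. If the eighth session falls at the end of the 16-week treatment window in Table 1, the follow-up falls at about 16 + 4 = 20 weeks. All 9 extra contacts can therefore fall within the trial period. Participants who leave therapy early will have fewer, hence up to 9.

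This counts trial contacts only. The Treatment as usual section describes case manager meetings, psychiatric support and, in TAU, possible one-to-one or structured work. Their number is not given, so 12 against 3 is not a ratio of detection.

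**Step 2: what unequal detection does to the ratio (detection rates assumed).** If the true AE rate is the same in both arms, the apparent ratio is d(CAT) / d(TAU), where d is the proportion of events detected. With d(CAT) = 0.9:
- d(TAU) = 0.8: 0.9 / 0.8 = 1.125
- d(TAU) = 0.6: 0.9 / 0.6 = 1.5
- d(TAU) = 0.4: 0.9 / 0.4 = 2.25

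In the other direction, at 0.9 against 0.6 a true one-third reduction in CAT gives 0.9 × 2/3 = 0.6, which equals TAU and looks like no difference.

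**Step 3: how often an excess would appear with no true difference.** Inputs: 30 per arm (Sample size); an assumed mean of 2 AEs per participant; Poisson counts. Expected count = 30 × 2 × d. Yardstick: z = (CAT − TAU) / √(CAT + TAU) > 1.96. This yardstick is chosen for illustration; the protocol sets none.

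| d(CAT) / d(TAU) | Expected events, CAT v TAU | P(z > 1.96), mean 2 AEs | Range, mean 1 to 3 AEs |
|---|---|---|---|
| 0.8 / 0.8 | 48 v 48 | 2.5% | 2.5% |
| 0.9 / 0.8 | 54 v 48 | 9% | 6–11% |
| 0.9 / 0.6 | 54 v 36 | 48% | 27–64% |
| 0.9 / 0.5 | 54 v 30 | 75% | 46–90% |

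Counting participants with at least one AE (assumed true proportion 50% in both arms) gives the same picture. At 0.9 against 0.6 the expected numbers are 30 × 0.5 × 0.9 = 13.5 and 30 × 0.5 × 0.6 = 9.0. A CAT excess of 6 or more participants then has probability 40%, against 7% when detection is 0.8 in both arms.

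**Step 4: what is already collected alike in both arms.** The SITBI is administered at 8, 16 and 20 weeks and the AEP questionnaire at 20 weeks (Table 2), by assessors intended to be blind to allocation. The article does not connect either of them to the AE imbalance or to its review.

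**The case against.** A reader might infer that an imbalance is the only safety trigger in the trial. The text does not support that. The research team reviews every SAE for a causal link, the TSC monitors SAE reports independently and receives AE updates at least quarterly, and SAEs attributed to trial procedures may lead to pausing or stopping. None of this depends on comparing arms. The imbalance is only the sole between-arm signal stated.

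A reader might also infer that the comparison has no usable reading at all. That goes too far. SITBI and AEP data are gathered on the same schedule in both arms and could serve as a check, and deaths, life-threatening events and admissions depend less on session attendance. Nor does the plan allow an excess to be ignored: it requires a review after conceding the detection effect, and the review is a judgement by informed people, with no formal test or automatic stop.

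Three further points carry weight. Routine care contacts are not counted, and because parallel high-intensity one-to-one therapy is contraindicated alongside CAT, TAU contacts may offset part of the gap. The detection rates are assumptions. And the AE form, data management plan and SAP are not shown, so a source field may exist; its absence from the article is not the point here.

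What stands is narrower. The article itself names unequal detection, and it states its between-arm signal without tying it to sources common to both arms. Acknowledging the difference does not give the reviewers a means of allowing for it.

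**Conclusion.** The point holds in a limited form. As written, the between-arm AE imbalance sent for review is open to unequal ascertainment that the protocol itself anticipates, and a reviewer cannot readily tell a true excess in CAT from extra detection. This concerns mainly non-serious AEs. SAEs are less affected, although the text applies its expectation of imbalance to both.

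The size cannot be derived from the documents. What they do support is up to 9 extra scheduled trial contacts in CAT on top of 3 shared assessments, with routine contacts unknown. The apparent ratios of 1.125 to 2.25 and the probabilities above rest on assumed detection and event rates; they show that the effect could matter and do not estimate it. With equal detection the expected ratio is 1.

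This is a worthwhile, inexpensive improvement to a feasibility trial whose other safety safeguards remain in place. It does not show that safety oversight fails.

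**What to change.** 1. Record the source of each AE: therapy contact, trial assessment, clinical record or service report.
2. Ask a standard AE question of both arms at the existing blinded 8-, 16- and 20-week assessments.
3. Give the TSC subgroup the between-arm comparison for shared-source events alongside the all-source counts, with SITBI and AEP data as a cross-check. List events found only at therapy sessions separately.
4. Keep the all-source count as a trigger for review, so that harms identified by therapists stay within it. Use the shared-source comparison to interpret any imbalance and as the main between-arm AE comparison in the report. Individual SAE review is unchanged.

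The cost is one case report form field, one question at visits already planned and one extra table. The shared-source comparison will contain fewer events and so be less precise. Asking about AEs may occasionally lead a participant to reveal allocation to an assessor; the plan already records such breaks and provides for a replacement assessor where possible.
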